### 8.3.9 Tissue biopsies

On CID 1 and 3, after the DEXA scan, tissue biopsies will be taken from abdominal subcutaneous adipose tissue (scAT) and skeletal muscle tissue (SMT). In both tissues, the expression of genes, proteins and pathways related to adipogenesis, lipid metabolism oxidative metabolism and inflammatory profile will be analysed by standard PCR and blotting methodologies. Biopsies will be taken in >10h fasting state.

*Adipose tissue biopsy*

An abdominal subcutaneous adipose tissue biopsy will be performed using needle biopsy to obtain approximately 1 gram of adipose tissue. After administering of local anesthesia (lidocaine 2%), a needle biopsy will be performed.

*Muscle tissue biopsy*

A skeletal muscle biopsy will be taken from the *m. vastus lateralis*. After locally administered anesthesia (lidocaine 2%), the skin and fascia will be opened using a small incision. Afterwards, the biopsy needle will be inserted into the muscle to obtain several muscle samples using suction. A total of approximately 100mg will be collected. After the biopsy, the site of insertion will be closed using a Steristrip® and bandaged with Tegaderm® and Acrylastic® pressure bandage.

Besides changes in SCFA receptor GPR41/43 expression in these tissues, signalling pathways involved in insulin signalling and oxidative metabolism (i.e. phosphorylation of IRS1, PKC and AMPK, as well as PGC-1 $\alpha$  and PPAR $\alpha/\gamma$ ), lipolysis (i.e. total and phosphorylated HSL, ATGL and its co-activator CGI-58 and PLIN1), and inflammation (i.e. NF $\kappa$ B, CD68, Interferon- $\gamma$  and MCP) will be analysed in these samples using RT-qPCR and/or Western Blot. In this project we will focus on adipose tissue and skeletal muscle metabolism, since alterations in adipose tissue and muscle functionality could play a key role in the SCFA induced improved peripheral insulin sensitivity, by affecting lipolysis and proinflammatory processes in adipose tissue and fat oxidation in skeletal muscle. Additionally, adipocyte size will be determined. If budget allows, untargeted gene sequencing will be performed.

**8.3.10 Two-step hyperinsulinemic-euglycemic clamp**

To assess whole-body and tissue-specific insulin sensitivity, we will be performing a two-step hyperinsulinemic-euglycemic clamp, which is the gold standard to determine insulin sensitivity. The clamp will be performed on CID 2 and 4 and will take place after a >12h overnight fasting period and a standardized meal the evening before. Before starting the procedure, an intravenous canula will be inserted in an antecubital vein to provide intravenous access for insulin and glucose suppletion. Another intravenous canula will be inserted on the dorsal side of the contralateral hand to ensure intravenous access for blood sampling.

At  $t = 0$  minutes, a fasting blood sample (10ml) will be drawn, followed by infusion of a primed 6,6-H2-glucose tracer at 0.04mg/kg/min, which will be used to calculate endogenous glucose production (EGP), glucose appearance (Ra) and glucose disposal. Therefore, blood samples (6ml) will be drawn at  $t=90$ , 105 and 120 min. At  $t = 120$ min, insulin will be infused at a low,

constant rate of 10 mU/m^2/min for 3 hours to allow determination of hepatic glucose production. After 3 hours ( $t = 300\text{min}$ ), insulin infusion will be increased to 40 mU/m^2/min to inhibit EGP for 2.5 hours, providing insight in muscle insulin sensitivity. During insulin suppletion, plasma glucose levels will be measured every 5 minutes (1ml), upon which glucose (20% glucose solution) will be infused at 10-30ml/h to ensure a constant plasma glucose level of 4.8-5.2 mmol/l during the clamp. Afterwards, the total amount of infused glucose can be used to determine insulin sensitivity. Additional blood samples (6ml) will be drawn at  $t = 180, 240, 270, 285, 400, 420, 435$  and 450 minutes.

At  $t = 450\text{min}$ , insulin infusion will be terminated and glucose infusion will be slowly reduced to zero to ensure a safe normalisation of glucose homeostasis. Additional dietary supplements will be provided (sandwiches, drinks) to prevent a hypoglycemic state.

During the clamp, an indirect calorimetry will be performed, which will be described below.

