#### 4.4 Sample size calculation

We used G-power to calculate the sample size required to detect a clinically relevant change in peripheral insulin sensitivity.

To calculate the sample size, we used the data derived from previous clinical trials of our research group using a comparable participant population to assess effects of alterations of the gut microbiota on peripheral insulin sensitivity with the hyperinsulinemic-euglycemic clamp technique. Based on the studies' data we calculated a within-group residual SD of 2.70, which was based on a SD of post measurement of 3.95 and a pre-post correlation of 0.73;  $\sqrt{(1-0.732)} \times 3.95 = 2.70$ . Twenty-two (we aim to include an equal number of males and females: 11

males and 11 females) participants per group (N = 44) are needed to detect a physiological relevant difference of 20% (2.86µmol/kg/min) in the change in our primary outcome parameter peripheral insulin sensitivity measured via the hyperinsulinemic-euglycemic clamp technique, assuming a power of 80%, an  $\alpha$ -value of .05, a within-group residual SD of 2.70 and a 20% dropout rate. The described secondary outcomes will be analysed exploratively, for microbiome analysis Benjamini-Hochberg procedure will be used to prevent false-positive results.

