### **7.6 Dosages, dosage modifications and method of administration**

Two-step hyperinsulinemic-euglycemic clamp:

- Insulin and glucose 20% (clamp): i.v. glucose 20% strongly dependent on the insulin sensitivity of the participant.
- [6,6-2H2]-glucose (clamp): i.v. prime concentration of 2.4 mg/kg body weight and a continuous infusion of 0.04 mg/kg/min for t = -120 to 330 minutes. The infusion will be set at a concentration that has no metabolic effect in humans (tracer amounts).
- Lidocaine (AT and skeletal muscle biopsies): 4-6 ml for local subcutaneous injection.

Gut permeability:

- 1 gram lactulose, 1 gram sucralose, 1 gram erythritol, 0.5 gram rhamnose for each administration. All will be dissolved in water and administered orally. No dosage modification is needed.

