### 10.1 Primary study parameter(s)

We will be comparing the intervention group versus the placebo group regarding the change in insulin sensitivity as measured by the two-step hyperinsulinemic-euglycemic clamp. Changes in glucose disposal rate and infused glucose concentrations before and after the 12 week intervention period are our primary study parameters and will be analysed and compared between the two groups. Data from both groups will be analysed using a linear mixed model to include repeated measures. An intention-to-treat and per-protocol analysis will be conducted. Intervention and study period will be set as fixed factors, participants will be set as random factor. Age and sex will be added as covariates in the analysis.

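### The glucose infusion range printed for the clamp (10-30 ml/h of 20% glucose) cannot hold the stated glucose target at the disposal level that the sample size calculation implies

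*Protocol*

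**What the plan says.** Section 8.3.10 describes two insulin steps, 10 mU/m²/min for 3 hours and then 40 mU/m²/min for 2.5 hours. The second is meant "to inhibit EGP for 2.5 hours, providing insight in muscle insulin sensitivity". One instruction on glucose covers both steps: while insulin runs, plasma glucose is checked every 5 minutes, and on that basis "glucose (20% glucose solution) will be infused at 10-30ml/h to ensure a constant plasma glucose level of 4.8-5.2 mmol/l during the clamp". The section adds that the total glucose infused can be used to determine insulin sensitivity, and that a tracer is used to calculate endogenous production, appearance and disposal.

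Section 7.6, on dosages, gives no numeric rate and describes the infusion as "i.v. glucose 20% strongly dependent on the insulin sensitivity of the participant".

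Section 4.4 says that 22 participants per group "are needed to detect a physiological relevant difference of 20% (2.86µmol/kg/min) in the change" in peripheral insulin sensitivity, using an "SD of post measurement of 3.95 and a pre-post correlation of 0.73" from the group's earlier clamp studies.

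Section 10.1 states: "Changes in glucose disposal rate and infused glucose concentrations before and after the 12 week intervention period are our primary study parameters".

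**The concern.** The 10-30 ml/h in section 8.3.10 is the only numeric glucose infusion rate in the protocol, and the sentence ties the five-minute titration to it. In a clamp with endogenous production suppressed, the rate needed to keep glucose constant is approximately the disposal rate, which is the quantity section 4.4 is planned on. If the top of the range lies far below that quantity, the range, the glucose target and the planning figures do not describe the same procedure.

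If the range were followed, glucose would fall below target while insulin continued. The euglycaemic steady state behind both primary parameters would be lost, and the recorded infusion rate would stop at a value that, per kilogram, reflects body weight more than insulin sensitivity. If staff exceeded the range to hold the target, the data would be sound, but the written procedure would not be the one carried out.

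**Working it through.** **Inputs**
- Infusion range, concentration and target: section 8.3.10.
- Effect of 2.86 µmol/kg/min, said to be 20%; post-measurement SD 3.95; pre-post correlation 0.73: section 4.4.
- BMI at least 28 and below 40: section 4.2.
- Assumed: height 1.60-1.80 m; 180.16 g/mol for glucose; roughly normal values; endogenous production suppressed in the second step, as section 8.3.10 intends.

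**The plan's own figures.** √(1 − 0.73²) × 3.95 = 2.70, which reproduces the residual SD. With 2.86 and 2.70, a two-sided t-test at 0.05 with 80% power needs 16 per group, and 16/0.80 = 20 after dropout, against the stated 22. That difference does not bear on this point, which uses only the implied mean and the SD of 3.95.

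**Step 1, what the range supplies.** 30 ml/h × 0.2 g/ml = 6 g/h = 100 mg/min; 100/180.16 × 1000 = 555 µmol/min. The lower end, 10 ml/h, supplies 185 µmol/min.

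**Step 2, what section 4.4 implies.** 2.86/0.20 = 14.3 µmol/kg/min.

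**Step 3, the weight at which these agree.** 555/14.3 = 38.8 kg. At BMI 28 that is a height of √(38.8/28) = 1.18 m, so no adult of usual height fits.

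**Step 4, over the admitted weights.** 28 × 1.60² = 71.7 kg and 40 × 1.80² = 129.6 kg. Supply per kg is 555/weight. The rate corresponding to 14.3 is 14.3 × weight/555 × 30 ml/h. The share above the range is the part of Normal(14.3, 3.95) above 555/weight.

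| Weight | Supplied at 30 ml/h (µmol/kg/min) | Rate matching 14.3 (ml/h) | Share above range |
|---|---|---|---|
| 72 kg | 7.7 | 55 | 95% |
| 90 kg | 6.2 | 70 | 98% |
| 130 kg | 4.3 | 100 | 99% |

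The third column is a consistency check, not a proposed rate.

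**Step 5, less favourable assumptions**
- Residual endogenous production of 1, 2 or 4 µmol/kg/min (assumed): at 90 kg the mean need is 65, 60 or 50 ml/h, and 96%, 94% or 85% exceed the range. With 4 µmol/kg/min the share is 73% at 70 kg and 92% at 120 kg.
- Unit per kg fat-free mass, which is not what section 4.4 writes (45-65 kg assumed): the mean need is 35-50 ml/h, and 69-93% exceed the range.
- Solution made from glucose monohydrate: 30 ml/h supplies 5.6 µmol/kg/min at 90 kg, so the gap widens.
- If 14.3 is a rise above basal disposal: basal disposal equals basal endogenous production, and insulin does not raise that production. The infusion needed is 14.3 + basal − residual production, which is at least 14.3.
- The tracer adds 0.04 mg/kg/min, or 0.04/180.16 × 1000 = 0.22 µmol/kg/min, too little to matter.

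The mean need exceeds 30 ml/h in every case.

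**The case against.** The strongest reply is that section 8.3.10 sets no cap. It never calls 30 ml/h a maximum; it makes plasma glucose the controlled quantity, measured every five minutes, and holding the rate while glucose fell would defeat the sentence's own purpose. Section 7.6 leaves the rate to the participant's insulin sensitivity. Section 11.4 refers to extensive experience with the clamp and to operating procedures for every measurement. The planning data in section 4.4 come from the group's own earlier clamps; if those imply a mean near 14.3, the group's practice was presumably not held to 30 ml/h, although section 4.4 does not give the insulin dose used there. The range may be loosely descriptive, or may have been meant for the low-insulin step.

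Most of this stands, and it rules out several stronger readings that a reader might infer:
- That the primary endpoint will be capped and a 2.86 µmol/kg/min difference cannot be seen. This requires staff to treat 30 ml/h as a hard stop against the stated target, and nothing in the protocol tells them to.
- That section 7.6 contradicts section 8.3.10. It is looser: a rate can depend on the participant and still lie within a range.
- That infused glucose is the primary measurement. Section 10.1 names it alongside glucose disposal rate, which section 8.3.10 obtains with the tracer.

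What the reply does not remove is the mismatch itself. The titration is written as taking place at 10-30 ml/h, no step is singled out, and no assumption examined brings the average participant within the range.

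**Conclusion.** The point holds as an inconsistency between the printed range, the printed glucose target and the level implied by section 4.4. At about 72-130 kg, 30 ml/h supplies roughly 30-54% of that level (4.3/14.3 to 7.7/14.3). About 95-99% of participants would exceed the range under the main assumptions, and about 70-95% under the less favourable ones.

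The direction is firm; the shares are not. The 14.3 is back-calculated, because section 4.4 does not say what the 20% is a percentage of. The weights rest on assumed heights, and the shares on normality and on how far endogenous production is suppressed.

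The consequence is conditional. If the range is followed, euglycaemia is lost or the infusion rate is truncated, and both feed the primary parameters. If it is not followed, the measurements may be sound, but nearly every clamp departs from the protocol. The documents do not show which would happen.

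**What to change.** Reconcile the range in section 8.3.10 with the 4.8-5.2 mmol/l target, with section 7.6 and with the level implied by section 4.4. State whether 10-30 ml/h is a starting range, a range for one insulin step, or a limit, and check the final wording against the body weights that the inclusion criteria admit. Which infusion rule is right is for the sponsor and the clinical team; none is proposed here.

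In section 4.4, it would help to state the mean behind the 20% and whether the 2.86 refers to infusion rate or to tracer-derived disposal.

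The cost is a one-sentence protocol amendment, with no added procedure, visit or participant.

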### 8.3.11 Indirect calorimetry

During the hyperinsulinemic-euglycemic clamp, an indirect calorimetry will be performed using a ventilated hood (Omnical, Maastricht Instruments, Maastricht). Measurements will take place during the basal, low insulin and high insulin infusion for 30 minutes (i.e. starting at  $t = 90, t = 270$  and  $t = 420$  minutes). During calorimetry, a hood will be placed over the subject's head to enable a continuous breath analysis for calculation of energy expenditure, and fat and carbohydrate oxidation. Data can then be used to determine resting metabolic rate, energy expenditure and total rate of fat and carbohydrate oxidation using the equations of Weir and Frayn.(46, 47) Nitrogen (N) excretion will be calculated based on the assumption that protein oxidation represents 15% of total energy expenditure. Additionally, urinary nitrogen will be analyzed as described before.

Calculations:

$$\text{Energy Expenditure (EE) (kJ/min)} = (3.9 \cdot \text{VO}_2) + (1.1 \cdot \text{VCO}_2)$$

$$\text{Carbohydrate oxidation (CHO) (g/min)} = (4.55 \cdot \text{VCO}_2) - (3.21 \cdot \text{VO}_2) - (2.87 \cdot \text{N})$$

$$\text{Fat oxidation (FAT) (g/min)} = (1.67 \cdot \text{VO}_2) - (1.67 \cdot \text{VCO}_2) - (1.92 \cdot \text{N})$$

$$\text{N (g/min)} = ((0.15 \cdot \text{EE})/17)/6.25$$

### 8.3.12 Questionnaires

Multiple questionnaires will be used during the study period. The moment some or all these questionnaires will be used, are upon entering the study before CID 1, in week 2, 6 and 9 and before CID 3. The following questionnaires will be used:

*Dietary habits*

A 3-day food record will be filled in regarding dietary intake over three random days in the week prior to CID 1 and 3 and in week 6 (one weekend day and two weekdays). A mobile phone application, produced by the Dutch organisation Voedingscentrum, called Eetmeter, will be used. All products and quantities will be specified as specific as possible. Data will be gathered on CID 1 and 3 and in week 6.

*Physical activity*

Physical activity will be measured using the SQUASH questionnaire. Participants will be asked to maintain their usual physical behaviour. To ensure the amount of physical activity remains constant throughout the study period, the questionnaire will be filled in upon starting the study, in week 6 and at the end. Participants should refrain from any strenuous physical activity during the study period ( $\geq 4$  hours per week).

*Gastrointestinal symptom rating scale (GSRS)*

To determine possible side effects due to the dietary components, the GSRS will be used. This questionnaire will be filled in at CID 1 and 3 and at week 2, 6 and 9 and contains information about the last 7 days, prior to the moment of measurement.

*Bristol stool scale*

The Bristol stool scale will be used alongside the GSRS at CID 1 and 3 and at week 2, 6 and 9 to determine possible changes in the consistency of produced faeces during the trial.

*Three-factor eating questionnaire (TFEQ)*

This questionnaire will be filled in to analyse neuropsychological responses to different types of food and food-related questions. 51 questions are divided in three subcategories: “cognitive restraint of eating”, “disinhibition” and “hunger” and will be scored on a binary scale.(41-43) The TFEQ will be filled in on CID 1 and 3.

*fMRI Image validation*

A small questionnaire, containing 30 of the 120 images (10 from each category) shown during the fMRI, will be filled in on or before CID1 to analyse to what extent the high- and low-calorie images are being liked and induce a feeling of hunger. This will be used to ensure that the hypothesized responses to the different food categories can be distinguished.

If applicable, some questionnaires can be filled in the day prior to CID 1 and 3.

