### 4.3 Exclusion criteria

A potential subject that meets any of the following criteria will be excluded from participation in this study:

- Diabetes mellitus (type 1 or 2)
- Cardiovascular disease: Including no history of myocardial infarction, heart failure, arrhythmias (except hypertension ( $< 160/100$  mmHg is allowed))
- Pulmonary disease: no history of chronic obstructive pulmonary disease, emphysema, bronchitis, asthma
- Kidney disease/failure
- Hepatic disease/failure
- Gastrointestinal disease or a history of abdominal surgery (except appendectomy and cholecystectomy): No inflammatory bowel disease, irritable bowel syndrome and related diseases.
- Any other diseases affecting glucose and/or lipid metabolism
- Malignancy (except non-invasive skin cancer)
- Auto-immune disease
- Major mental disorders preventing correct participation (such as severe depression, psychosis, schizophrenia)
- Ongoing (infectious) disease or any disease with a life expectancy  $\leq 5$  years

- Substance abuse (nicotine abuse (including e-cigarettes) defined as >20 cigarettes per day; alcohol abuse defined as  $\geq 8$  drinks/week for females and  $\geq 15$  drinks/week for males(38); any drugs)
- A change in weight  $\geq 3$ kg over the last 3 months or plans to lose weight or follow a hypocaloric diet during the study period
- Pre/pro/antibiotic use in the last 3 months or during the study
- Use of medication that influences glucose or fat metabolism and inflammation, such as:
  - o Use of statins (stable use  $\geq 3$  months prior to and during study is allowed)
  - o Use of antidepressants (stable use  $\geq 3$  months prior to and during study is allowed)
  - o Use of anticoagulants (acetylsalicylic acid and carbasalate calcium are allowed)
  - o Use of medication known to interfere with study outcomes
  - o Use of  $\beta$ -blockers
  - o Chronic corticosteroid treatment (>7 consecutive days)
- Regular use of laxatives 3 months prior to the study or during study period
- Change in physical activity or diet during study period
- Intensive physical activity (>3h per week)
- Pregnancy
- Following a vegan or vegetarian diet; presence of food allergies, intolerances or diet restrictions interfering with the study.

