## 5. TREATMENT OF SUBJECTS

### 5.1 Investigational product/treatment

All participants will receive a high-protein diet during the entire trial (12 consecutive weeks in total, starting the day directly after CID 2 until the day prior to CID3). This diet will consist of 25 energy percentage (E%) protein, 30E% fat and 45E% carbohydrates. Proteins will be 45-50% plant-based and 50-55% animal-based, to ensure a resemblance to the current western diet consisting of mainly animal-based proteins, while simultaneously acting on the currently shifting trend in society towards more plant-based diets.

Furthermore, according to randomization, one group will receive a potato-pectin fibre mixture and the remaining participants will receive a placebo.

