### 8.3.14 Dietary intervention

At the end of CID 2, participants receive the assigned intervention (potato-pectin fibre mixture or placebo), in a blinded manner to both the participant and original investigator. Participants will start using the dietary supplement the day after CID 2 and continue to do so for 84 consecutive days. The assigned supplement should be consumed thrice daily during breakfast, lunch and dinner. Along with the dietary supplement, all participants should consume a diet high in proteins (see below). This diet will be composed in collaboration with a dietician to provide a diet suitable to each individual's needs and taste. Furthermore, subjects are asked to consume  $\leq 1$  alcohol units/day, based on the national dietary guidelines.(53)

Additionally, all participants will follow a diet high in proteins alongside the dietary supplement, of which the exact composition will be discussed individually to establish a diet suited to the participants' needs and taste. The energy requirements for this diet will be estimated using indirect calorimetry. The diet will consist of 25 energy percentage (E%) protein mixture, 30E% fat and 45E% carbohydrate. Proteins will be 45-50% plant-based and 50-55% animal-based, to ensure a resemblance to the current western diet consisting of mainly animal-based proteins, while simultaneously acting on the currently shifting trend into more plant-based protein-rich components.

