#### **8.4.1 Specific criteria for withdrawal**

Apart from the opportunity for the subject to leave the study at any moment, a participant will also be withdrawn from the study in case of any situation making continuing of the study unsafe. Also, if one of the exclusion criteria is met during the study, withdrawal will follow.

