### 11.4 Benefits and risks assessment, group relatedness

In general, obesity and its related diseases bring a high burden to a patients wellbeing and quality of life. Furthermore, these diseases are one of the leading causes of death worldwide, have a high socio-economic impact on society, and thus increase health care costs. By evaluating possible strategies to improve metabolic, gut and brain health, we want to attribute to a healthier lifestyle, a decrease in obesity and obesity-related diseases and in the socioeconomic impact of said diseases.

By testing the pre-established, possibly beneficial dietary component, we will gain insight in specific metabolic pathways, analyse interactions between food, gut and brain, and find potential ways to steer the human digestive system to provide beneficial substrates and reduce detrimental by-products. Along with the purpose of finding fundamental evidence to support further preventative or therapeutic interventions and studies, participants might benefit individually from the intervention in terms of small short-term improvements in body weight, body composition and carbohydrate, fat metabolism and emotional wellbeing.

Nor the investigated dietary additive, placebo or high-protein diet will pose any risk to general health in participants, since these are natural, commonly used dietary components and possible allergies or intolerances are established and ruled out during the screening visit. However, they might cause mild gastro-intestinal discomfort. Furthermore, adhering to a diet for 12 consecutive weeks, consisting of relatively high amounts of proteins and the investigated fibre-combination, requires motivation, compliance, time and willingness to change their normal lifestyle behaviour to a temporary lifestyle compliant with the prescribed intervention. This will subsequently pose a burden to participants, which is necessary to be able to evaluate the effects on primary and secondary outcome parameters as stated in chapter 8.

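### The activity limit is >3 h per week in the exclusion criteria but ≥4 h per week in the in-study instruction, and 8.4.1 turns the gap into mandatory withdrawals that lose the final clamp

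*Protocol*

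**What the plan says.** Two sections of the protocol put a number on physical activity. Among the exclusion criteria, section 4.3 lists "Intensive physical activity (>3h per week"). Under Physical activity, section 8.3.12 asks participants to refrain from "strenuous physical activity during the study period ( $\geq 4$ hours per week"). The same paragraph, like section 5.2, asks participants to keep their activity at its usual level, and schedules the SQUASH questionnaire at the start, in week 6 and at the end to check this.

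Section 4.3 also has a separate bullet, "Change in physical activity or diet during study period". Yet section 5.1 says "All participants will receive a high-protein diet during the entire trial", section 8.3.14 repeats that "all participants will follow a diet high in proteins alongside the dietary supplement", and section 11.4 says participation requires "willingness to change their normal lifestyle behaviour to a temporary lifestyle compliant with the prescribed intervention".

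Section 8.4.1 extends the exclusion criteria into the study period: "if one of the exclusion criteria is met during the study, withdrawal will follow". Section 8.6 then says that a withdrawn participant needs no follow-up unless there is a medical reason. Section 10.1 plans both an intention-to-treat and a per-protocol analysis of the change in clamp insulin sensitivity, and section 8.3.10 places the clamps on CID 2 and CID 4.

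**The concern.** Taken alone, the two figures could be read as one threshold for entry and another for conduct. Section 8.4.1 closes off that reading, because it makes the 4.3 figure a withdrawal rule for the whole study, in mandatory terms. Participants are thus told one limit and can be withdrawn under a lower one.

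Staff will have answers to apply these limits to: section 8.3.15 says the questionnaires serve to determine adherence to the diet and activity restrictions.

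What is at stake is the primary outcome. A withdrawal for exceeding an activity limit is not medical and happens after randomisation. If no follow-up is needed, the second clamp is not done. An intention-to-treat comparison is meant to include randomised participants whatever their adherence. A rule that removes them for a lifestyle breach, and stops measuring them, works against that aim. The losses would also depend on behaviour after randomisation, so they cannot safely be assumed unrelated to outcome.

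**Working it through.** No figure in the plan needs to be reproduced here; the check is a comparison of sections.

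**Step 1: the two activity limits, by weekly hours**

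| Reported activity | 4.3 criterion (>3 h) | 8.3.12 limit (≥4 h) | Under 8.4.1 |
|---|---|---|---|
| up to 3 h | not met | not reached | stays in |
| more than 3 h, less than 4 h | met | not reached | withdrawn |
| 4 h or more | met | reached | withdrawn |

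The sections disagree only in the middle row, a band one hour wide. Only 4.3 governs withdrawal, since 8.4.1 refers to the exclusion criteria and 8.3.12 attaches no withdrawal consequence of its own. The contradiction is therefore between the limit that participants are given and the limit at which they are withdrawn.

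**Step 2: what withdrawal costs**

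- SQUASH is completed before CID 1, in week 6 and before CID 3 (8.1.3).
- A breach found in week 6, or before CID 3, precedes the second clamp on CID 4 (8.3.10).
- 8.4.1 requires withdrawal, and 8.6 requires no further follow-up without a medical reason.
- The participant then has a baseline clamp but no final clamp, so the change in insulin sensitivity (8.1.1) is not observed.
- Section 10 would fill the gap by multiple imputation. That replaces a measurement that could have been taken with an assumption about why it is missing.

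**Step 3: the diet bullet**

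- 4.3 names any change in diet during the study period and states no exception.
- 5.1 and 8.3.14 assign a new diet to everyone, and 11.4 acknowledges that this changes normal behaviour.
- No section says that the assigned diet does not count. The evident intention is a change other than the assigned diet, but the text does not say so. Staff have no written test for which dietary departures trigger 8.4.1.

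**The case against.** The strongest reply is that the sections agree more than the two numbers suggest. Anyone enrolled was at or below 3 h per week at entry. Moving to 3.5 h is normally an increase, which departs from the request in 8.3.12 and 5.2 for constant activity and meets the separate 4.3 bullet on change in activity. The 4 h figure is an instruction to refrain, not a licence to go up to 4 h. This stands in large part, and it narrows the practical conflict mainly to people who start near 3 h and drift slightly above it. It does not remove the conflict: the only number participants are given for the study period is still higher than the one that triggers withdrawal.

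Second, 4.3 says intensive and 8.3.12 says strenuous, and if hours were counted whole the two limits would coincide. The protocol defines neither word and does not say how hours are counted, so the ambiguity remains open.

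Third, section 8.5 allows a withdrawn participant to be replaced, and section 10 provides imputation. Replacement can restore the headcount, but not the outcome of the person who was randomised. Imputation does not supply the missing measurement.

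A reader might infer more from the diet bullet: that all 44 participants must be withdrawn once the diet starts, or that nobody could be adherent in the per-protocol analysis. The documents do not support either. Adherence is judged in 8.3.15 against the prescribed diet, so no one would apply the bullet that way. Section 10.1 names the per-protocol analysis without defining its set, and that definition may properly sit in a statistical analysis plan.

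**Conclusion.** The point holds as a contradictory activity threshold feeding a mandatory withdrawal rule, with the avoidable loss of the final clamp as its consequence. The missing exception for the assigned diet is a lesser drafting slip in the same list.

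The size is unknown and probably small. The documents give no distribution of physical activity, so the share of participants between 3 and 4 h per week cannot be estimated. A reader might infer a material loss of power, but any such figure would rest on an invented share, and 8.5 permits replacement. The case rests on inconsistent withdrawal and missing primary outcomes after randomisation, not on power.

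The conclusion assumes that 8.4.1 is applied as written, and that 8.6 is read as allowing the final visits to be omitted after a non-medical withdrawal. If staff would in practice still perform CID 3 and CID 4, the loss does not occur, but the protocol does not say that they will.

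**What to change.** - Reconcile 4.3, 8.3.12 and 8.4.1 to one activity figure and one term for the kind of activity meant. Which figure is for the sponsor to decide.
- Add to the 4.3 bullet on change in activity or diet an exception for the assigned study diet.
- State in 8.4.1 and 8.6 that participants who breach these lifestyle criteria after randomisation are still invited to CID 3 and CID 4, so that their outcomes enter the intention-to-treat analysis, and that the breach is handled in the per-protocol analysis. This concerns outcome collection only.

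The cost is a wording amendment. It adds no participants and no visits beyond those already scheduled.
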